### Assignment of intervention and randomisation

Patients should be screened as soon as the tumour stage (UICC II-III) is confirmed and the neoadjuvant therapy (chemoradiation or 5×5 Gy schedule) has been defined. All patients having undergone neoadjuvant therapy for clinically staged cT3/4 Nx or cTx N+ rectal cancer (staged with endorectal ultrasonography + CT or endorectal ultrasonography + MRI), LAR with TME and protective stoma and after having given written informed consent will be registered for the trial. The randomisation will take place around 7 days after LAR by central online registration, after exclusion of anastomotic leakage by endoscopy and/or radiographic enema. Patients will be allocated to two groups, early group (experimental) - stoma closure between day 8 and 10 after LAR before starting the adjuvant chemotherapy and late group (standard) - stoma closure after adjuvant chemotherapy around week 26 after LAR. A central computer-generated block-randomisation with alternating block sizes will be performed by web-randomisation within the electronic case report forms (eCRF) system in order to ensure an adequate random allocation. There will be stratification by centre.

### Interventions and trial flow

The stoma may be closed either by a direct suture of the anterior wall or by an end-to-end, side-to-side or end-to-side anastomosis after a segmental resection of the bowel (stapler or hand suture) according to the centre’s standard of care.

The following 5-FU- and oxaliplatin-based adjuvant chemotherapy schedules are allowed:four cycles of bolus 5-FU 500 mg/m^2^ (days 1–5, repeated at day 29) or bolus 5-FU 350 mg/m^2^ plus folinic acid 20 mg/m^2^ (days 1–5, repeated at day 29),five cycles of capecitabine 2500 mg/m^2^ (days 1–14, repeated at day 22),XELOX-Schedule – five cycles of capecitabine 2000 mg/m^2^ (days 1–14, repeated at day 22) plus oxaliplatin 130 mg/m^2^ (day 1, repeated at day 22),De Gramont-Schedule – eight cycles of bolus 5-FU 400 mg/m^2^ (day 1, repeated at day 15) plus 5-FU 600 mg/m^2^ over 24 h (days 1 and 2, repeated at day 15) plus folinic acid 200 mg/m^2^ (day 1, repeated at day 15),FOLFOX6-Schedule – eight cycles of bolus 5-FU 400 mg/m^2^ (day 1, repeated at day 15) plus 5-FU 2400 mg/m^2^ over 46 h (day 1, repeated at day 15) plus folinic acid 400 mg/m^2^ (day 1, repeated day 15) plus oxaliplatin 85 mg/m^2^ (day 1, repeated at day 15).

In both arms, adjuvant chemotherapy starts within 4 (earliest) and 12 (latest) weeks after randomisation, unless unexpected complications occur. Each participating institution should preferably select one of the regimens for their patients, before randomisation, in order to avoid bias. When a regimen has been started in an individual patient, this regimen should be continued throughout the study period. Administration of chemotherapy and regular blood tests as well as the treatment of adverse events (AEs) will be done according to the standard operating procedure implemented in the various oncological departments. Concomitant therapies (e.g. antiemetics) are allowed in accordance to local standard treatment but dose reduction should be done according to the protocol and to NCI-CTCAE criteria v.4.03 [20] unless it is not in the best interest of the treated patient (Table 2). Concurrent administration of any other anti-cancer therapy is not permitted during trial participation. The treatment and prophylaxis of some AEs such as neuropathy [21], hand-foot skin reaction [22], antiemetic treatment [23], chemotherapy induced diarrohea [24], and high-output stoma [25] should be performed according to the international standards.

**Table 2 Tab2:** Dose modification scheme adapted to severity of adverse events

	Grade 2	Grade 3	Grade 4
1. occurrence	Withold therapy until AE has resolved to grade 0–1.	Withold therapy until AE has resolved to grade 0–1.	Withold therapy until AE has resolved to grade 0–1.
	Continue with 100 % of the starting dose.	Continue with 75 % of the starting dose	Continue with 50 % of the starting dose
2. occurrence	Withold therapy until AE has resolved to grade 0–1.	Withold therapy until AE has resolved to grade 0–1.	Stop treatment.
	Continue with 75 % of the starting dose.	Continue with 50 % of the starting dose.	
3. occurrence	Stop treatment	Stop treatment	

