## Methods/Design

### Trial design

CoCStom is an investigator-initiated prospective randomised open-label multicentre trial with two parallel study groups.

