### Outcome measures and definitions

CoC is defined as primary endpoint and can be assessed objectively immediately after completion of treatment. CoC will be measured 28 weeks after randomisation. This point of time reflects the status after planned complete chemotherapy administration in both trial groups and after the stoma has already been closed.

CoC will be assessed by determining the proportion of the randomised patients which complete all planned cycles of adjuvant chemotherapy. Secondary endpoints and their definition are presented in Additional file 3.

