### Statistical methods

#### Sample size calculation

The sample size calculation is based on the analysis of the primary endpoint, completeness of adjuvant chemotherapy. According to our recent randomised phase III trial on perioperative treatment of stage II and III rectal cancer, a total of 61.7 % (capecitabine) and 57.5 % (5-FU), respectively, started adjuvant chemotherapy, and 45.7 and 40.0 % had their scheduled cycles completed [14]. These data are consistent with the findings in other studies investigating perioperative chemo (radio)therapy in rectal cancer.

Based on this data, we assume a CoC rate of 42 % for the standard patient group with a diverting stoma during adjuvant chemotherapy. A 20 % absolute increase of CoC (42–62 %) is regarded as a clinically meaningful step forward. In order to significantly detect this difference on a type I error level of 5 % (two-sided) with a power of 80 %, a sample size of 107 is required in each arm based on the application of Fisher’s exact test. The Mantel-Haenszel procedure stratifying for centre will be used for the primary hypothesis of the trial.

Any major deviation from these CoC rate assumptions will lead to increased power, if the delta of 20 % is retained. According to the primary endpoint, the number of losses in the intention-to-treat (ITT) population should be minimal. A rate of 10–20 % of drop-outs and losses to follow-up is expected. Thus, about 260 patients should be randomised to ascertain sufficient power in the per-protocol analysis. Stratification by centre is foreseen, since centre-specific characteristics such as the quality of surgery, patient guidance with respect to chemotherapy compliance, etc. may have a major influence on important outcome parameters.

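### Choosing the adjuvant regimen before randomisation is asked for only as a preference, so the planned cycles that define the primary endpoint can be set knowing the arm; the risk is real, its size and direction unknown

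*Protocol article*

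**What the plan says.** All references are to the protocol article.

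- **Endpoint** (Outcome measures and definitions): CoC is the "proportion of the randomised patients which complete all planned cycles of adjuvant chemotherapy".
- **Regimens** (Interventions and trial flow): bolus 5-FU has four cycles, capecitabine and XELOX have five, De Gramont and FOLFOX6 have eight. XELOX and FOLFOX6 contain oxaliplatin; the others do not.
- **Choice of regimen** (same section): "Each participating institution should preferably select one of the regimens for their patients, before randomisation, in order to avoid bias".
- **When it becomes fixed** (same section): "When a regimen has been started in an individual patient, this regimen should be continued throughout the study period". On timing: "In both arms, adjuvant chemotherapy starts within 4 (earliest) and 12 (latest) weeks after randomisation".
- **Blinding** (Trial design): "CoCStom is an investigator-initiated prospective randomised open-label multicentre trial with two parallel study groups".
- **Stratification**: randomisation (Assignment of intervention and randomisation) and the Mantel-Haenszel test (Sample size calculation) use centre only. The example covariates for the logistic model (Analysis variables and statistical methods) do not include regimen.

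**The concern.** The regimen is a co-treatment and also defines success, because a patient is complete or not relative to the schedule that was planned. The article recognises that choosing it after allocation could bias the comparison, then makes the safeguard a preference. Preferably may qualify one regimen per institution, or the timing before randomisation. On either reading neither is required, and the firmer rule applies only once treatment has started.

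By then the arm is known and, according to the legend of Fig. 1, early-arm stomas have been closed since about two days after randomisation. The article itself gives reasons why stoma status might enter the choice. It lists high-output stoma and chemotherapy-induced diarrhoea among the events to be managed, and the Background says that low anterior resection syndrome after reversal may aggravate side-effects of chemotherapy.

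If the regimen mix then differs between arms and the regimens differ in tolerability, part of the CoC difference reflects regimen and not closure timing. Intention-to-treat analysis keeps patients in their arm but does not make the regimen mix equal. Adjusting for a regimen chosen after allocation would mean adjusting for a post-randomisation variable, and that does not restore the randomised comparison.

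**Working it through.** **1. The plan's own figure.** Inputs from Sample size calculation: 42% against 62%, two-sided 5%, power 80%. The mean rate is 0.52.

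- Uncorrected n per arm = [1.96·√(2·0.52·0.48) + 0.8416·√(0.42·0.58 + 0.62·0.38)]² / 0.20² = 96.8, so 97.
- With continuity correction, n = (96.8/4)·[1 + √(1 + 4/(96.8·0.20))]² = 106.5, so 107, as stated.
- Exact power of Fisher's test at 107 per arm is 79.6%.

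The sample size reproduces and is not in question here.

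**2. Gap between regimens that the article documents.** In the earlier phase III trial, for capecitabine and 5-FU respectively, 61.7% and 57.5% started adjuvant chemotherapy and "45.7 and 40.0 % had their scheduled cycles completed".

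- Overall gap: 45.7 − 40.0 = 5.7 points.
- Among starters: 45.7/61.7 = 74.1% against 40.0/57.5 = 69.6%, a gap of 4.5 points.
- About 60% started, so the starters' gap is worth 0.60 × 4.5 = 2.7 points of overall CoC.

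The overall gap already contains a 4.2-point difference in starting (61.7 − 57.5), so 2.7 to 5.7 points is a reasonable bracket.

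**3. Shift in the CoC difference.** Shift = gap × between-arm difference in regimen share. The article gives no figure for the second factor. With 30 points (assumption):

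- 0.30 × 2.7 = 0.8 points
- 0.30 × 5.7 = 1.7 points

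**4. False-positive rate.** Normal approximation, unstratified, 128 per arm (257/2), control rate 42%, no true effect of timing: 5.2% for a shift of 0.8 points and 5.9% for 1.7 points, against 5.0% with no shift.

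**5. Range over the assumed imbalance.** Overall gap of 5.7 points, exact Fisher test at 128 per arm. The last column takes the shift as acting against the early arm when the true rates are 42% and 62%.

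| Difference in regimen share | Shift (points) | False-positive rate | Power |
|---|---|---|---|
| 0 | 0 | 3.7% | 87.7% |
| 25 points | 1.4 | 4.2% | 82.3% |
| 50 points | 2.9 | 5.8% | 75.6% |
| 100 points | 5.7 | 12.5% | 59.1% |

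The last row is a bound: every patient in one arm on one drug and every patient in the other arm on the other.

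**6. Does the cycle count itself matter?** Planned length is 4 × 28 = 112 days, 5 × 21 = 105 days and 8 × 14 = 112 days. Completing all cycles means nearly the same treatment time under each schedule.

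**The case against.** The strongest reply is that the rule is already there. The article states the intended practice, gives the reason and asks that a started regimen be kept. Where a centre follows it, centre-stratified randomisation and testing balance the regimen by design. That stands for single-regimen centres, but nothing obliges a centre to be one.

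A second reply is that this is a condensed article, and the full protocol or the eCRF may already capture the intended regimen before allocation. That cannot be seen. What can be judged is the rule as printed, which identifies a bias and leaves its prevention optional. If the full protocol is stricter, only the article's sentence needs aligning.

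A third is that the only documented gap is weak evidence. It comes from a comparison of two drugs over the whole perioperative treatment and partly reflects who started. This stands and is why the size is given as a bracket.

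A reader might go further and infer serious inflation of the type I error. If schedules with and without oxaliplatin differed by 15 to 20 points in CoC, a 30-point imbalance would shift the difference by 4.5 to 6.0 points and raise the false-positive rate to about 11 to 16%. The article does not support this. Neither the gap nor the imbalance is given. With about 60% of patients starting, such a gap would also need 25 to 33 points among starters (15/0.60 and 20/0.60).

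A reader might also infer that a four-cycle plan is an easier target than an eight-cycle plan. The near-equal planned lengths speak against that; the issue is differing tolerability together with arm-dependent choice.

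**Conclusion.** The point holds as a risk of bias in the confirmatory endpoint, not as a demonstrated bias. It rests on the printed text: optional selection before allocation, an open-label design, a regimen fixed only at treatment start, and an endpoint defined by the planned cycles.

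Size and direction are unknown. On the documented gap and an assumed 30-point imbalance, the shift is about 0.8 to 1.7 points against a 20-point target, and the false-positive rate is about 5 to 6%. A shift the other way would cost power instead. Larger effects need either near-complete separation of regimens by arm or gaps that the article does not give. The calculations ignore stratification, which would reduce the shift further where centres use one regimen. The change is worth making because it is cheap and because the protocol itself says that the safeguard serves to avoid bias.

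**What to change.** 1. Replace the preference with a requirement: the intended regimen (centre default or patient-specific) and its number of cycles are entered in the eCRF before the web randomisation is released. Randomisation already runs inside the eCRF system, so this is one mandatory field.
2. Define planned cycles in the endpoint by that entry.
3. Leave clinical choice unrestricted. Record any later change of regimen with its reason, and score it by one prespecified rule applied equally in both arms. For example, a switch counts as complete only if the full course of the replacement schedule, as prespecified, is given, with a sensitivity analysis counting switches as not complete. Holding a switched patient to the cycle number entered at randomisation would misclassify: someone moving from a four- to an eight-cycle schedule would be complete halfway, and someone moving from eight to five could never be complete.
4. Report intended and delivered regimen by arm.
5. Trial status gives 75 patients randomised by 28 August 2015, leaving 257 − 75 = 182 (71%) of the target to come under the new rule. For the 75, use a documented pre-randomisation choice where one exists, and report where none does.

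The cost is that sites must name the intended regimen by about day 7 after resection. The sample size is unaffected.

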### Description of the trial visits

Trial visits will be performed in the corresponding clinical centres (surgical and oncological departments). Examples for trial visits for chemotherapy regimen with eight cycles are given as Additional file 1 and Additional file 2.

### Outcome measures and definitions

CoC is defined as primary endpoint and can be assessed objectively immediately after completion of treatment. CoC will be measured 28 weeks after randomisation. This point of time reflects the status after planned complete chemotherapy administration in both trial groups and after the stoma has already been closed.

CoC will be assessed by determining the proportion of the randomised patients which complete all planned cycles of adjuvant chemotherapy. Secondary endpoints and their definition are presented in Additional file 3.

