**Fig. 1 Fig1:**
[figure not shown]
Expected patient flow from screening to final analysis. Early closure group: stoma closure and first chemotherapy (CTx) will be done around 2 days and within 4 (earliest) to 12 (latest) weeks respectively after randomisation. Late closure group: first CTx will be done within 4 (earliest) to 12 (latest) weeks after randomisation; stoma closure will be done 4 weeks after end of CTx. Randomisation will be performed around day 7 after LAR (after exclusion of an anastomotic leakage). To reach the statistically calculated goal of 257 recruited patients, at least 128 patients have to be randomised into each trial arm. W: weeks, M: months, OP: operation, *: after randomisation

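### The week-28 reading of completeness of chemotherapy does not cover the protocol's own start window plus delays, its stated rationale is untrue for later-starting late-arm patients, and scoring of patients still on treatment is not fixed

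*Protocol article*

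**What the plan says.** Under Outcome measures and definitions, CoC is the "proportion of the randomised patients which complete all planned cycles of adjuvant chemotherapy". That definition has no time limit. The same section sets a date, "CoC will be measured 28 weeks after randomisation", and gives the reason: "This point of time reflects the status after planned complete chemotherapy administration in both trial groups and after the stoma has already been closed".

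Interventions and trial flow sets the start: "In both arms, adjuvant chemotherapy starts within 4 (earliest) and 12 (latest) weeks after randomisation, unless unexpected complications occur". It allows regimens of four 28-day cycles, five 21-day cycles or eight 14-day cycles. Table 2 answers a first grade 2, 3 or 4 event and a second grade 2 or 3 event with "Withold therapy until AE has resolved" to grade 0–1, and gives no maximum duration.

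For the late arm, the Fig. 1 legend states "stoma closure will be done 4 weeks after end of CTx". Assignment of intervention and randomisation instead places that closure at about 26 weeks after the resection, with randomisation about 7 days after it.

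The primary analysis treats patients who drop out or have missing data as failures. It does not mention patients who are still receiving cycles. The main analysis is to run once post-operative therapy is documented for everyone, at about 7 months.

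**The concern.** The date and the definition agree only if everyone who completes chemotherapy has done so by week 28. The protocol's own start window, cycle lengths and open-ended holds do not guarantee this. For some protocol-compliant patients the endpoint would then be whether all cycles were given by a date, not whether they were given.

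This matters because the start of chemotherapy is something the intervention can shift. Early closure is an additional operation before chemotherapy. The Background accepts that its complications may impair chemotherapy, and the start rule lets complications postpone it. A fixed date can turn such postponement into non-completion, possibly more often in one arm. The Abstract lists delay as a secondary endpoint separate from completion, and a date-limited reading mixes the two.

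The rationale given for the date also conflicts with the schedule for late-arm closure.

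**Working it through.** **Inputs (protocol article).** Start in weeks 4–12; cycle numbers and lengths from Interventions and trial flow; closure 4 weeks after the end of chemotherapy (Fig. 1 legend); reading at week 28; planning rates 42% and 62% with 107 per arm (Sample size calculation).

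**Formulas, in weeks.** Last dose = start + [(cycles − 1) × cycle length + dosing days] / 7. Cycle end = start + cycles × cycle length / 7. Late-arm closure = either of these + 4, since the legend does not say which counts as the end of chemotherapy. Slack = 28 − last dose.

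**The plan's own figure.** Latest start plus longest regimen is 12 + 16 = 28. Week 28 is thus the end of the longest undelayed course, with nothing left for holds or for the 4-week closure interval. The article does not say how the date was chosen.

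**Start at week 12, no delay:**

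| Regimen | Weeks from start to last dose | Last dose | Cycle end | Closure from last dose | Closure from cycle end | Slack |
|---|---|---|---|---|---|---|
| 5-FU bolus, 4 × 28 d | 89/7 = 12.7 | 24.7 | 28 | 28.7 | 32 | 3.3 |
| Capecitabine or XELOX, 5 × 21 d | 98/7 = 14.0 | 26.0 | 27 | 30.0 | 31 | 2.0 |
| De Gramont, 8 × 14 d | 100/7 = 14.3 | 26.3 | 28 | 30.3 | 32 | 1.7 |
| FOLFOX6, 8 × 14 d | 101/7 = 14.4 | 26.4 | 28 | 30.4 | 32 | 1.6 |

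**Closure.** With a week-4 start, closure counted from cycle end falls at week 23–24, so the permitted range is week 23–32. Closure by week 28 needs a start by week 8–9 counted from cycle end (28 − 4 − 16 or 15), or by week 9.6–11.3 counted from last dose. Closure 26 weeks after resection is about week 25 after randomisation. Counted from cycle end, that fits only a start near week 5–6 (25 − 4 − 16 = 5; 25 − 4 − 15 = 6).

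**Completion.** A patient who eventually receives every cycle is incomplete at week 28 only with:
- a week-12 start and cumulative holds above 1.6–3.3 weeks;
- a start beyond week 13.6–15.3 without holds (28 − 14.4; 28 − 12.7); or
- a week-4 start and holds above 9.6–11.3 weeks.

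**Illustration under assumptions that are not in the documents.** Take starts uniform over weeks a to b, total hold exponential with mean m, and an 8-cycle regimen with last dose 14.3 weeks after start. The share of completers missed is [m / (b − a)] × [exp(−(13.7 − b)/m) − exp(−(13.7 − a)/m)].
- Starts in weeks 4–12: m = 1 gives about 2%, m = 2 about 10%, m = 3 about 20%.
- With m = 2: starts in weeks 4–8 give 2.5%, weeks 6–10 give 7%, weeks 8–12 give 18%.
- Strong contrast, early arm starting in weeks 8–12 and late arm in weeks 4–8: 62% × 0.82 = 50.8% and 42% × 0.975 = 41.0%. The 20-point difference shrinks to about 10 points.

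**Power.** The stated 107 per arm is reproduced by the continuity-corrected formula for 42% versus 62%; exact enumeration of Fisher's test gives 79.6% power. If 10% of completers were missed equally in both arms (37.8% versus 55.8%), power would be 70.1%. If they were missed only in the early arm (42% versus 55.8%), it would be 46.1%. The 10% is an assumption.

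**The case against.** The strongest reply is that week 28 is a nominal visit, not a cut-off. The definition of CoC has no time limit, the article says CoC can be assessed as soon as treatment is complete, and the main analysis waits for documentation of therapy in all patients at about 7 months (about 30.4 weeks). A patient still on treatment is neither a drop-out nor missing. A reader might infer that the failure rule counts such a patient as a failure, but the article does not say so. This part stands: the handling is left open, not stated wrongly. It does not remove the point, because the confirmatory endpoint then has two readings that differ for exactly these patients.

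A reader might also infer that a late start alone costs a completer the endpoint. It does not: inside the window, without delay, the last dose is given by week 26.4. The treatment-free end of the last cycle runs to week 28, but no dose falls there.

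Nor does stoma closure after week 28 affect scoring, since closure is not part of the CoC definition.

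Finally, the rates of missed completers rest on assumed inputs. Table 2 stops treatment at a third grade 2 or 3 event or a second grade 4 event, so those patients are not completers, and a hold that resolves before the next scheduled dose need cause no delay. Both arms have the same start window, and nothing documents a difference in start between them.

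**Conclusion.** The point holds in limited form and should be fixed. Two things follow from the article's own figures without further assumptions. First, the statement that the stoma is already closed at week 28 is untrue for late-arm patients starting after about week 8–9 (week 9.6–11.3 if counted from last dose), and it does not fit the other closure-timing statements. Second, a compliant patient with a late start plus roughly 2–3 weeks of cumulative holds, or with a start well beyond week 12, can receive all cycles yet be incomplete at week 28, with no rule for scoring.

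How often this happens cannot be read from the article. The range of about 2–20% of completers on 8-cycle regimens depends on uniform starts and mean total holds of 1–3 weeks. Attenuation of the effect requires the start delay to differ by arm. A reader might go further and infer a reversed effect; even the strong contrast above leaves about 10 points in the same direction, so reversal is not shown.

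**What to change.** - Define CoC as all planned cycles administered, read when each patient's adjuvant treatment is documented as ended. Alternatively, set an outer cut-off of 12 + 16 = 28 weeks plus a stated allowance for holds and complication-related late starts.
- State how a patient still on treatment at the cut-off is scored.
- Keep the week-28 reading as a sensitivity analysis, and report the time from randomisation to first dose by arm.
- Correct the sentence saying that the stoma is closed by week 28. The sponsor should reconcile the timing statements in the Fig. 1 legend, Assignment of intervention and randomisation, Interventions and trial flow, and Outcome measures and definitions.

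The cost is protocol and analysis-plan wording, one date field in the eCRF, and a main analysis a few weeks later at most. No change to treatment is proposed.
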